From 2003, the INSERM UMR1052 radiobiology group has elaborated a collection of primary skin fibroblast lines from patients (the majority of adults) with DNA repair deficiencies or who experienced RT toxicity on various tissues, with various severity and different post RT free intervals. The RT-induced distribution of candidate DSB recognition and repair proteins was measured with an indirect immunofluorescence (IIF) assay [13, 14] leading to a general classification of Human IRS based on the rate of unrepaired DSB 24 h after ex vivo irradiation (γH2AX marker). This last study showed further that a delay in the nucleoshuttling of the pATM protein, which is involved in the recognition of the DSB, was a common feature to patients with overreaction (OR) [15]. The maximal number of pATM foci between 10 min and 1 h post irradiation (pATM_max_) was found to be the parameter with the best correlation with each OR severity grade, independently of tumor localization and of the early or late nature of reactions. When taken as a binary predictive assay with the optimal cut-off value of 35 pATM foci, pATM_max_ foci showed promising predictive performances on a retrospective study, with an AUC of 0.97, a PPV of 99%, a specificity of 92% and a sensitivity of 100% [16].

We designed a prospective open-label, non-randomized multicenter cohort study to address the distribution of IRS and validate the performance of the IRS assay in the pediatric subpopulation. We will prospectively recruit 222 children/adolescents who require RT as part of their care path and follow them during 15 years to describe the specific morbidity including second malignancies. Prior RT we will collect blood and skin samples to raise a primary dermal fibroblast line to carry out the IRS assay – the result of which will have no impact on the RT prescription.

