## Methods/design

### Aim, design and setting

#### Objectives

ARPEGE aims to explore the distribution of IRS in the pediatric population and to determine prospectively the discriminating ability of an IRS assay to predict the occurrence of early cutaneous, mucosal or hematological RT toxicity qualified as unusual in children/adolescents treated with RT for cancer.

The short term secondary objectives consist in: 1) identifying thresholds for each biomarker to predict the occurrence of unusual early toxicity in order to define IRS groups, 2) comparing the discriminating ability of IIF biomarkers (pATM and γH2AX on the one hand and micronuclei on the other hand), 3) developing a multivariate predictive model combining biomarkers.

The long-term secondary objectives consist in: 1) identifying the discriminating ability of biomarkers to predict the occurrence of Grade 3–4 late toxicities, and thresholds for each biomarker, 2) describing IRS biomarkers in the subset of patients developing secondary malignancies, 3) investigating the correlation between the severity of early toxicity and the occurrence of late toxicity (including secondary malignancies).

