#### Endpoints

The primary endpoint is the skin fibroblast radiosensitivity defined as the residual DSB 24 h after ex vivo radiation assessed with IIF (γH2AX marker). Unusual early cutaneous, mucosal or hematological toxicity occurs within 3 months after RT and is defined by any of the following features appreciated with CTCAE v4.0 morbidity scale:Grade 2 or higher occurring at low doses (first week of treatment) orGrade 3–4 for more than 4 weeks after completion of RT and / or requiring surgery [17].

The discriminating ability of this biomarker to predict the occurrence of early toxicity will be assessed by the area under the receiver operating characteristic (ROC) curve.

Kinetic data on other DSB repair proteins are collected in order to refine the classification of IRS as secondary endpoints. The other biomarkers studied are therefore: 1) the number of pATM foci 10 min and 1 h post irradiation, 2) the average number of micronuclei per cell 24 h after irradiation (control IRS assay).

Late toxicity including second malignancies occurs at least 3 months after the completion of RT. Severe sequelae are defined by any grade 3–4 adverse effect with a progression lasting more than 90 days [17].

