### Statistical analysis

#### Statistical methods

The discriminating ability of any IIF biomarker to predict the severity of toxicity will be defined by the area under the ROC (AUC) curve as well as its 95% confidence interval. The following hypothesis: H_0_: AUC ≤ 0.7 against H_1_: AUC > 0.7 will be tested.

The discriminating capacity of biomarkers will be compared by the nonparametric Mann-Whitney approach [19]. For each biomarker, the choice of the optimal threshold will be determined using the Youden index to maximize both sensitivity and specificity. The sensitivity and specificity of each biomarker will be compared by a Mac Nemar test. A multivariate logistic regression will be carried out on all biomarkers with a level of significance less than 0.2 in bivariate analyses. The simplification of this model will be carried out by a logistic multivariate regression with a downward selection at significance level 0.2 [20] using the bootstrap re-sampling method [21]. The discriminating capacity of the model will be estimated using the area under the ROC curve (95% confidence interval). The correlation between early and late toxicity will be evaluated with a Chi-Squared or Exact Fisher test.

The analysis of the main and secondary short-term objectives is planned as soon as all the included patients have 3 months of follow-up. Intermediate analysis of the long-term secondary objectives will be carried out at 2, 5 and 10 years.

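### The one-at-a-time p < 0.2 entry screen for the combined biomarker model is unnecessary with about four readings, and can drop a reading that is informative mainly jointly with a correlated one

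*Protocol article*

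**What the plan says.** In the protocol article, the Objectives section lists as the third short-term secondary objective "developing a multivariate predictive model combining biomarkers". The Statistical methods section sets the entry rule: "A multivariate logistic regression will be carried out on all biomarkers with a level of significance less than 0.2 in bivariate analyses". That model is then simplified by "a downward selection at significance level 0.2", with bootstrap resampling. No clause keeps the two pATM readings together or exempts any marker from the screen.

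The candidates are in the Endpoints section: γH2AX at 24 h (the primary marker), "the number of pATM foci 10 min and 1 h post irradiation", and "the average number of micronuclei per cell 24 h after irradiation (control IRS assay"). That makes about four post-irradiation readings. The same section explains why the secondary markers are measured: "Kinetic data on other DSB repair proteins are collected in order to refine the classification of IRS as secondary endpoints".

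The Background says two things about pATM. The feature common to over-reacting patients was "a delay in the nucleoshuttling of the pATM protein". The measure that tracked severity most closely, however, was a maximum: "The maximal number of pATM foci between 10 min and 1 h post irradiation (pATM_max_) was found to be the parameter".

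**The concern.** A one-at-a-time test asks whether a reading differs between children with and without unusual toxicity when everything else is ignored. A combined model asks whether it adds information given the others. For correlated readings the two answers can differ. A reading that hardly differs between the groups can still sharpen prediction, because it shows how far its partner departs from what is expected for that child. Two counts of the same protein in the same cell line, at 10 min and 1 h, are an obvious candidate pair.

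The screen comes before the multivariable step, and the later selection works only downward, so such a reading cannot return. At stake is the quality of the combined model, whose declared purpose is to use the markers together.

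**Working it through.** **1. The plan's own figures.** Inputs from Power calculation and Statistical methods: AUC 0.85 against 0.70, 15% events, one-sided 2.5%, power above 0.8, 222 patients including 10% lost. Evaluable: 222 × 0.90 = 199.8, about 200. Events: 0.15 × 200 = 30, leaving 170 non-events.

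Hanley-McNeil variance: V(A) = [A(1−A) + (n1−1)(A/(2−A) − A²) + (n0−1)(2A²/(1+A) − A²)]/(n1·n0).
- A = 0.70: V = 16.23/5100, SE 0.0564.
- A = 0.85: V = 10.51/5100, SE 0.0454.
- Power = Φ[(0.15 − 1.96 × 0.0564)/0.0454] = Φ(0.87) = 0.81.

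The plan's sample size is reproduced. With four candidate readings there are 30/4 = 7.5 events per candidate.

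**2. Chance that one reading passes the screen.** For a standardized shift d, SE = √(1/30 + 1/170) = 0.198, P(pass) = Φ(d/SE − 1.28) + Φ(−d/SE − 1.28), and own AUC = Φ(d/√2).

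| d (SD) | own AUC | passes | dropped |
|---|---|---|---|
| 0 | 0.50 | 20% | 80% |
| 0.1 | 0.53 | 26% | 74% |
| 0.2 | 0.56 | 40% | 60% |
| 0.25 | 0.57 | 50% | 50% |
| 0.3 | 0.58 | 60% | 40% |
| 0.5 | 0.64 | 89% | 11% |
| 0.7 | 0.69 | 99% | 1% |

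A reading is more likely dropped than kept only when its own AUC is below about 0.57.

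**3. Cost when one pATM reading is marginally null.** The documents give neither shifts nor correlations, so all values here are assumptions. Cohorts had about 30 events and 170 non-events, and AUC was evaluated on new subjects.

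(a) The two pATM readings only, 10 min shifted by −1 SD and 1 h not shifted:

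| correlation | 1 h passes screen | 1 h has p < 0.2 jointly | AUC screened | AUC joint | loss |
|---|---|---|---|---|---|
| 0.3 | 21% | 57% | 0.758 | 0.762 | 0.004 |
| 0.5 | 20% | 93% | 0.765 | 0.792 | 0.027 |
| 0.7 | 22% | 99.9% | 0.780 | 0.840 | 0.060 |

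(b) All four readings, with γH2AX +0.8 SD, 10 min pATM −0.6, 1 h pATM 0 and micronuclei +0.5. Here the plan's full rule (screen, then downward selection) is compared with fitting all four:

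| correlation | AUC, plan | AUC, all four | loss |
|---|---|---|---|
| 0.3 | 0.774 | 0.778 | 0.004 |
| 0.5 | 0.771 | 0.781 | 0.010 |
| 0.7 | 0.773 | 0.799 | 0.026 |
| 0.85 | 0.787 | 0.848 | 0.061 |

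Downward selection started from the full four-reading model gave 0.795 at correlation 0.7 and 0.846 at 0.85. Most of the loss there therefore comes from the screen and not from the later selection. Further runs of this kind put the loss at correlation 0.85 between about 0.04 and 0.06.

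**4. Cases where little or less is lost.**
- Partial catch-up in (b), 1 h shift −0.2: dropped in 60–63% of cohorts, loss 0.001–0.009. In (a) with −1 and −0.2: differences of −0.001, 0.003 and 0.024 at correlations 0.3, 0.5 and 0.7.
- Both readings lowered equally (−0.6) in (b): the 1 h reading is dropped in 4–5%. AUC is 0.771–0.777 under the plan and 0.776–0.783 with all four.
- Risk driven by pATM_max: both readings pass in 99–100% of cohorts when their levels are similar, and in 81–100% when the 1 h level is 1 SD lower. Retention falls to 32–50% only when the 1 h level is 2 SD lower and the readings are uncorrelated. There the 10 min reading alone nearly equals the maximum (AUC 0.82 against 0.83, and 0.94 against 0.95).

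**5. A case in between.** With opposite shifts of −0.5 and +0.5 SD in (a), each reading passes in about 89% and both in about 78%. The average loss is 0.731 − 0.715 = 0.016, 0.763 − 0.739 = 0.024 and 0.820 − 0.780 = 0.040 at correlations 0.3, 0.5 and 0.7.

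**The case against.** A reader might infer that the pATM signal is a contrast between 10 min and 1 h, so that the screen tends to throw away the assay's key information and the study would then report that pATM kinetics add nothing. The documents do not support this. The Background speaks of a delay but does not define the predictor as a difference. It names the maximum as the best parameter, with a retrospective AUC of 0.97, and under a maximum both readings usually pass or the dropped one adds little. Nor is a one-at-a-time screen blind to every contrast: with opposite half-SD shifts both readings survive in about 78% of cohorts. The 80% drop rate is what a 0.2 threshold does to any marginally null marker; it says nothing specific about pATM.

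Three further objections carry weight. The article does not say whether pATM enters as two readings, as the maximum or as another summary; with a single summary this pATM example falls away. The smaller gains lie well inside the standard error of an AUC near 0.8 in this cohort, about 0.05, so the study could not itself demonstrate them. And a lenient 0.2 screen is conventional.

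What remains is that the screen is stated as a fixed rule and the Endpoints section lists two separate pATM readings. Sampling error in an estimated AUC does not make a weaker selection rule neutral on average. The screen brings no visible benefit with so few candidates.

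**Conclusion.** The point holds as an avoidable weakness in the analysis of short-term secondary objective 3. The screen can, but need not, discard a jointly informative reading. For a reading with own AUC between 0.50 and 0.57, the drop rate is about 80% falling to 50%. If it is marginally null, the average loss in out-of-sample AUC is about 0.004 at correlation 0.3 and up to about 0.06 at correlations of 0.7 to 0.85. With partial catch-up the differences were mostly below 0.01. When both readings shift alike or risk follows pATM_max, there is little or no loss. These sizes rest on assumed shifts and correlations that the documents neither give nor rule out.

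The primary AUC test of γH2AX, the sample size of 222 and each marker's own AUC and threshold do not depend on the screen.

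**What to change.** In Statistical methods, delete the bivariate p < 0.2 entry step. Enter all pre-specified biomarker readings jointly as continuous variables, and start the planned bootstrap downward selection from that full model. State in the same sentence how pATM enters (two readings, or one named summary such as the maximum). Shrinkage of the coefficients is optional.

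This changes wording only and needs no new data; it should be settled before outcomes are analysed. The cost is carrying one or two uninformative coefficients. With one pure-noise marker the AUC cost was about 0.001, and the largest shortfall of joint entry in any two-reading run shown was 0.003 (0.754 against 0.757, shifts −1 and −0.3, correlation 0.3).

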### Power calculation

If we hypothesize an area under the ROC curve of 0.85 for the main endpoint, a 15% occurrence of early toxicity [22] and a risk of first specie at 2.5% then 222 patients are necessary to obtain a power greater than 0.8 including 10% of lost to follow-up. Thirty unusual early and late toxicities are therefore expected.

According to inter-regional data updated in 2015, the inclusion potential would be 150 patients per year in the territory.

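### Secondary objectives: Youden cut-offs and the selected model are evaluated on the roughly 30 events used to derive them, with no stated optimism correction

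*Protocol article*

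**What the plan says.** The Objectives section of the protocol article lists, among the short-term secondary objectives, "identifying thresholds for each biomarker to predict the occurrence of unusual early toxicity in order to define IRS groups", a comparison of the biomarkers, and the development of a multivariate model.

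The Statistical methods section carries these out in one cohort:

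- Each biomarker's threshold is the Youden optimum, and the biomarkers' sensitivities and specificities are then compared by a McNemar test.
- Biomarkers below p = 0.2 in bivariate analysis enter a logistic model, which is simplified by a "logistic multivariate regression with a downward selection at significance level 0.2" with bootstrap resampling. The bootstrap belongs to that simplification sentence.
- The next sentence gives the performance measure: "The discriminating capacity of the model will be estimated using the area under the ROC curve (95% confidence interval".

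The section names no split sample, external data set, cross-validation or optimism correction.

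The primary analysis is separate. The Endpoints section fixes one continuous marker, residual γH2AX foci at 24 h, judged by its AUC. The hypothesis in Statistical methods is "H_0_: AUC ≤ 0.7 against H_1_: AUC > 0.7 will be tested", stated for the AUC of the immunofluorescence biomarkers.

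**The concern.** A cut-off chosen to maximise sensitivity plus specificity in a sample fits that sample's noise, and so does a model whose terms were selected there. Performance read back from the same patients is apparent performance and is biased upwards. The usual confidence interval treats the cut-off or model as given and ignores the search. With about 30 events, sensitivity suffers most, because it is estimated from the events alone.

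At stake are the secondary results that readers will want to use: the thresholds meant to define radiosensitivity groups, their sensitivity and specificity, and the combined model's AUC. A sensitivity reported as 81% that is really 74% means that 26% rather than 19% of the children with unusual toxicity fall below the cut-off.

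**Working it through.** **Inputs from the protocol article.** AUC 0.70 under the null hypothesis (Statistical methods). From Power calculation: "If we hypothesize an area under the ROC curve of 0.85 for the main endpoint"; "a 15% occurrence of early toxicity"; type I error 2.5%, taken as one-sided because the alternative is AUC > 0.7; and "222 patients are necessary to obtain a power greater than 0.8 including 10% of lost to follow-up".

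**Step 1: events.** 222 × 0.90 = 199.8 evaluable patients; 199.8 × 0.15 = 29.97. The simulations therefore use 30 events and 170 non-events.

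**Step 2: the plan's own sample size.** This is a one-sample AUC test with Hanley-McNeil variance:

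Var(A) = [A(1−A) + (n1−1)(Q1−A²) + (n0−1)(Q2−A²)] / (n1·n0), where Q1 = A/(2−A) and Q2 = 2A²/(1+A).

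- A = 0.70: (0.21 + 29 × 0.0485 + 169 × 0.0865)/5100 = 0.00318, SE 0.0564.
- A = 0.85: (0.1275 + 29 × 0.0166 + 169 × 0.0586)/5100 = 0.00206, SE 0.0454.
- Power = Φ[(0.15 − 1.96 × 0.0564)/0.0454] = Φ(0.87) = 0.81.

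Solving for power 0.80 gives 197 evaluable patients, or 219 after dividing by 0.9. The binormal variance gives 198 and 220. The stated 222 reproduces, so the primary sizing is sound.

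**Step 3: Youden cut-off.** Assumption (not in the document): equal-variance binormal markers. In each simulated cohort the Youden cut-off is found. Its sensitivity (Se) and specificity (Sp) are then read in that cohort (apparent) and from the known distributions at the same cut-off (true).

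| True AUC | Apparent Se / Sp | True Se / Sp | Excess in Se |
|---|---|---|---|
| 0.70 | 0.700 / 0.664 | 0.617 / 0.652 | 0.083 |
| 0.75 | 0.735 / 0.699 | 0.657 / 0.689 | 0.078 |
| 0.80 | 0.774 / 0.737 | 0.701 / 0.727 | 0.073 |
| 0.85 | 0.812 / 0.781 | 0.744 / 0.773 | 0.068 |
| 0.90 | 0.855 / 0.830 | 0.794 / 0.823 | 0.061 |

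Specificity is overstated by about 1 point. A nominal 95% exact interval for sensitivity covers the true value about 92% of the time at AUC 0.85 and 91% at 0.75.

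Positive predictive value at 15% prevalence and AUC 0.85 (second simulation run):

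- Apparent: 0.15 × 0.810/(0.15 × 0.810 + 0.85 × 0.216) = 0.40.
- True: 0.15 × 0.741/(0.15 × 0.741 + 0.85 × 0.226) = 0.37.

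**Step 4: selected model.** Screen at p<0.2, backward selection at 0.2, four candidates matching the four biomarkers in Endpoints (γH2AX at 24 h, pATM at 10 min and at 1 h, micronuclei at 24 h). Marker AUCs and correlations are assumptions.

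| Marker AUCs | Correlation | Apparent minus true AUC |
|---|---|---|
| 0.85, 0.70, 0.70, 0.70 | 0.5 | 0.012 |
| 0.85, 0.80, 0.80, 0.75 | 0.5 | 0.017 |
| all 0.85 | 0.5 | 0.016 |
| 0.85, 0.80, 0.80, 0.70 | 0.6 | 0.017 (0.876 against 0.858) |
| 0.75, 0.70, 0.70, 0.65 | 0.6 | 0.022 |
| all 0.70 | 0.5 | 0.032 (other runs up to 0.039) |

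**Step 5: what a correction achieves.** At AUC 0.85, repeating the Youden search in bootstrap resamples moves the reported sensitivity from 0.810 to 0.765, against a true 0.741. That removes (0.810 − 0.765)/(0.810 − 0.741) = 0.65 of the bias. At AUC 0.75 it removes (0.734 − 0.683)/(0.734 − 0.652) = 0.62. A cut-off fixed in advance shows no such bias: 0.769 against a true 0.768.

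**Step 6: primary analysis.** The AUC of one pre-specified marker averages 0.8501 when the truth is 0.85. There is no optimism.

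**The case against.** The best defence has four parts.

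- **The affected quantities are secondary and worded as development.** This is right. A reader might infer that the validation result itself will be inflated. It will not: the primary analysis is the AUC of a single marker named in advance, with no fitted cut-off or model.
- **The article condenses a fuller protocol, and the bootstrap may already be meant to correct the model's AUC.** This is possible and limits certainty about the model. But the article fixes the screening level, selection level, threshold rule and performance measure, and it ties the resampling to simplification. Nothing links the bootstrap to the Youden cut-offs.
- **The McNemar comparison gives every marker the same search, so the bias largely cancels.** This stands for the comparison: two equally good markers (AUC 0.85, correlation 0.5) showed a mean sensitivity difference of 0.0003. It does not rescue the absolute sensitivity and specificity of each threshold.
- **The model's optimism is small.** This stands near the protocol's own AUC of 0.85: 0.01 to 0.02 against a sampling SD of 0.03 to 0.04. Larger values, about 0.05, arise if seven weak measurements compete. That count includes the pre-irradiation readings, whereas Endpoints lists four biomarkers.

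**Conclusion.** The point holds for the secondary objectives only. Followed as written, the plan yields apparent performance. Sensitivity at the Youden cut-off is too high by about 6 to 8 points over true AUCs of 0.70 to 0.90, which is material. Specificity is too high by about 1 point. The model's AUC is too high by about 0.01 to 0.02 with a lead marker at 0.85, and by about 0.03 if four markers each have 0.70; this is modest but always favourable. The sizes rest on binormal markers, the assumed correlations, and 30 events among 200 evaluable patients.

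Two further readings are tempting but unsupported. One is that the optimism bears on the 0.7 benchmark: that test is stated for individual biomarkers, not for the model or any cut-off. The other is that later dose-adaptation trials will rest on these cut-offs: the Discussion says only that such trials will integrate individual radiosensitivity, not that they will use these thresholds or this model.

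**What to change.** In Statistical methods:

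1. Extend the planned bootstrap so that each resample repeats the p<0.2 screen, the backward selection and the Youden search. Report optimism-corrected AUC, sensitivity and specificity with bootstrap intervals. If the full protocol or analysis plan already intends this, say so.
2. Label the Youden cut-offs exploratory, because the correction removes only about two thirds of the sensitivity bias.
3. Also report sensitivity and specificity at the 35-foci pATM cut-off given in the Background. It was set in other data, so it needs no correction, and the 10 min and 1 h counts from which the pATM maximum is taken are already collected.

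Dropping the p<0.2 screen or penalising the model would be a matter of preference and is not needed. The cost is computing time, some wording, and slightly less favourable reported figures. Neither data collection nor the sample size changes.

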### Anticipated completion of enrollment

All patients should be included over a 30-month period. The duration of follow-up is 3 months after the completion of the RT for the main objective and 15 years for the secondary objectives. The overall duration of the study is therefore 17.5 years.

Our current expectation is that the final patient will be enrolled by July 2019, and the entire study will be completed by July 2033. Cumulative enrollment reached 10 cases as of August 2017.

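### Late toxicity over 15 years is given tests that ignore time, loss to follow-up and competing death, and the grade 3–4 wording leaves fatal late toxicity out

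*Protocol article*

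**What the plan says.** All references are to the protocol article.

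- **Early versus late toxicity** (Statistical methods): "The correlation between early and late toxicity will be evaluated with a Chi-Squared or Exact Fisher test". This serves the third long-term objective, which relates the severity of early toxicity to late toxicity, second malignancies included, with no grade limit.
- **Biomarkers versus late toxicity** (Objectives, first long-term objective): "identifying the discriminating ability of biomarkers to predict the occurrence of Grade 3–4 late toxicities, and thresholds for each biomarker". Statistical methods gives only one way to measure discrimination: "The discriminating ability of any IIF biomarker to predict the severity of toxicity will be defined by the area under the ROC (AUC) curve". No time-dependent or censoring-adjusted version is named.
- **Severe late events** (Endpoints): "Severe sequelae are defined by any grade 3–4 adverse effect with a progression lasting more than 90 days".
- **Horizon** (Anticipated completion of enrollment): "15 years for the secondary objectives". Statistical methods adds: "Intermediate analysis of the long-term secondary objectives will be carried out at 2, 5 and 10 years".
- **Deaths and losses**: the Background speaks of 80% survivors, and the Power calculation allows 10% lost to follow-up. Neither figure is tied to the 15-year horizon. No section says how a child who dies or is lost before a late event is classified.

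**The concern.** A contingency table and an ordinary ROC curve both require a settled yes or no for each patient. Over 15 years that status is unknown for anyone lost early, and it can no longer arise in anyone who has died. The analyst must either score these children 'no' or drop them. The first understates late risk when there is loss. The second overstates it, because events that happened early are kept while unfinished event-free follow-up is thrown away. If death or loss is related to early toxicity or to the biomarker, the comparison itself is also distorted.

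The grade wording is a separate matter. The Background motivates the study with a 30-year figure (42.4%) that includes specific death, yet the late biomarker endpoint and severe sequelae stop at grade 4. The worst late outcomes then have no place among the events that the assay is meant to predict. The Discussion foresees later trials that adapt dose to radiosensitivity, so late thresholds and risks estimated here may be reused.

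**Working it through.** **The plan's own figure first.** The sample size concerns only the 3-month endpoint. Inputs (Statistical methods; Power calculation): AUC 0.70 versus 0.85, 15% cases, alpha 2.5% taken as one-sided, power 0.80, 10% lost. The Hanley–McNeil variance is

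V(A) = [A(1−A) + (n1−1)(Q1−A²) + (n0−1)(Q2−A²)] / (n1·n0), with Q1 = A/(2−A) and Q2 = 2A²/(1+A).

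Solving 1.96·√V(0.70) + 0.84·√V(0.85) ≤ 0.15 gives 197, and 197/0.9 gives 219. The Obuchowski binormal variance gives 198, hence 220. Power with 200 evaluable patients (30 cases) is 0.808 and 0.805. So 222 reproduces closely. No size or power is stated for the late analyses.

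**How much follow-up may be incomplete.** If 20% deaths and 10% loss both applied over 15 years and independently (assumption), 222 × (1 − 0.8 × 0.9) = 62 children (28%) would die or be lost within 15 years. Some of them would have had a late event first.

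**Absolute risk.** Assumptions: constant hazards, 30% net 15-year late risk, 20% deaths over 15 years, loss rate l per year.

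- h = −ln(0.70)/15 = 0.02378; d = −ln(0.80)/15 = 0.01488
- Observed events: P = h/(h+d+l) × (1 − exp(−15(h+d+l)))
- Event-free with complete follow-up: S = 0.70 × 0.80 × exp(−15l)
- Scored 'no': P. Dropped: P/(P+S).

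| Loss | Scored 'no' | Dropped | Events missed if scored 'no' |
|---|---|---|---|
| none | 27.1% | 32.6% | 0 (this is the true cumulative incidence) |
| 10% over 15 years (l = −ln(0.9)/15 = 0.0070) | 25.8% | 33.9% | 1 − 25.8/27.1 = 5% |
| l = 0.02 (26% over 15 years) | 23.7% | 36.4% | 1 − 23.7/27.1 ≈ 12% |
| l = 0.04 (45% over 15 years) | 20.9% | 40.5% | 1 − 20.9/27.1 ≈ 23% |

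Without loss, scoring deaths 'no' gives the correct cumulative incidence. The shortfall in the fourth column comes entirely from loss.

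**Early–late comparison with no true effect on the late hazard.** Take the same h in both groups, l = 0.02, and deaths of 50% with early toxicity (d = 0.0462) versus 20% without.

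| Rule | Early toxicity | No early toxicity |
|---|---|---|
| Scored 'no' | 19.6% | 23.7% |
| Dropped | 19.6/(19.6+25.9) = 43% | 23.7/(23.7+41.5) = 36% |
| Cumulative incidence, no loss | 22.1% | 27.1% |

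The apparent association reverses with the handling rule. The third row shows that most of the first row's gap reflects competing death. Cumulative incidence has the same gap, and only the cause-specific hazard is equal in the two groups.

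**Test behaviour.** Simulation with 1,500 replicates, N = 222, 15% early toxicity, exponential times and 10% loss over 15 years:

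| Late risk (none / early) | Deaths (none / early) | Fisher, 'no' | Fisher, dropped | Log-rank, cause-specific |
|---|---|---|---|---|
| 30% / 30% | 20% / 20% | 0.03 | 0.03 | 0.04 |
| 30% / 30% | 15% / 45% | 0.06 | 0.06 | 0.05 |
| 30% / 50% | 20% / 20% | 0.49 | 0.46 | 0.57 |
| 30% / 50% | 15% / 45% | 0.24 | 0.62 | 0.57 |

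Entries are rejection rates at 0.05. In the second row the average crude risks, early versus none, are 22% versus 27% when scored 'no' and 39% versus 33% when dropped. The 0.62 in the last row is partly that same upward bias.

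**Grade wording.** Read literally, a late toxicity that is fatal with no earlier qualifying grade 3–4 record is neither a grade 3–4 late toxicity (Objectives) nor severe sequelae (Endpoints). A toxicity already recorded at grade 3–4 for long enough before death does count.

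**The case against.** A reader might infer that deaths and drop-outs are to be counted as free of late toxicity. The article does not say that. Exclusion is equally open and biases absolute risk upward. The handling rule is also a detail that an article commonly leaves to an analysis plan, so its absence alone would be no finding. What stands is that the methods themselves are named here, and neither can use partial follow-up under any rule.

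A reader might also infer that fatal toxicities become negatives in the chi-squared or Fisher test. That is not supported: the objective it serves has no grade limit. The grade problem belongs to the biomarker objective and to severe sequelae.

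The differential-death example can be over-read too. Its gap when incomplete patients are scored 'no' is mainly competing death and would appear in cumulative incidence as well. Type I error is barely affected: 0.03 when death is unrelated to early toxicity and about 0.06 when it is strongly related. What remains is lower power, understated or overstated absolute risk, and an estimated association whose direction depends on the rule.

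The inputs are soft. The 80% survival figure has no time horizon and does not describe this curative-intent radiotherapy cohort, and annual loss of 2–4% is heavier than the 10% in the Power calculation. Staggered entry adds little: 30 months of accrual plus 15 years gives the stated 17.5 years, so every child is meant to reach 15 years. The calendar dates (last enrolment July 2019, completion July 2033) allow only 14, a separate inconsistency to reconcile.

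**Conclusion.** The point holds for the long-term secondary objectives. The article fixes a contingency-table test and an ordinary AUC for outcomes that accrue over 15 years with deaths and losses, and these methods give biased or less precise late results. On the stated assumptions, scoring incomplete patients 'no' misses about 5% of events at 10% total loss and 12–23% at 2–4% annual loss, while dropping them raises 27.1% to between 34% and 41%. Power for the early–late association is 0.49 or 0.46 against 0.57 for a censoring-aware test when deaths are balanced. When deaths differ by early toxicity, the direction of bias depends on a rule that is not stated. No figure is put on the AUC, because it would rest on a marker model that the article does not give.

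The grade 3–4 wording does leave fatal late toxicity outside the late biomarker endpoint and severe sequelae. A reader might extend either point to the main result, but the documents do not support that: the 3-month primary analysis, its early-toxicity definition and N = 222 are untouched.

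**What to change.** In the protocol and analysis plan, replace the methods for the long-term objectives as follows.

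- Analyse late toxicity as time to first event from a landmark 3 months after radiotherapy, censoring at last contact.
- For the early–late association, use cause-specific Cox regression. Comparing cumulative incidence alone would still mix in differences in mortality.
- For absolute risk, report cumulative incidence with death as a competing event.
- For biomarkers, report time-dependent AUC with inverse-probability-of-censoring weights at 2, 5, 10 and 15 years, and derive late thresholds from these.
- Define the late endpoint and severe sequelae as grades 3–5, with fatal late toxicity an event whatever its duration. Leave the early definition as it is.

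The cost is wording and slightly more analysis work; no extra visits or patients are needed. One limit remains: visits are yearly for five years and then two-yearly, and the article does not say that onset dates are recorded. Event times may therefore be known only to the visit interval. Recording onset dates, or an interval-censored sensitivity analysis, would deal with this.
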